**Figure 1 fig1:**
[figure not shown]
Flowchart of the randomized controlled trial.

The following main hypotheses are investigated:

#### Primary outcomes

1.3.1

*H1:* Music intervention benefits language development.

It is expected that the music intervention group will show larger improvements in language abilities and neural speech processing between the baseline and post-intervention time points compared to the control intervention group. Language development will be evaluated with standardized parental questionnaires (validated parental report instruments), where a greater increase in the questionnaire scores is expected between the baseline and post-intervention assessments in the experimental (music) compared to the control arm (circus). Speech processing will be evaluated with ERPs and MMRs to speech sounds and their changes. ERPs and MMRs are hypothesized to display a more mature pattern in the experimental (music) than the control arm (circus) after but not prior to the intervention.

#### Secondary outcomes

1.3.2

*H2:* Benefits of the music intervention are long-lasting.

It is expected that the experimental arm will show superior language abilities and more mature/enhanced neural speech processing compared to the control arm still at the 1-year follow-up assessment. In addition to the outcome measures listed in H1, the hypothesis will be probed with a standardized language test at post-intervention and follow-up assessments.

#### Other/exploratory outcomes

1.3.3

*H3:* Intervention benefits depend on the age and developmental stage of the infants.

It is explored how infants’ age and important developmental milestones, such as walking without support and uttering first words at the start of the intervention, moderate the benefits on language development. For example, the benefits for neural speech sound processing may be larger the younger the infants start the music intervention (Kuhl, 2010); on the other hand, older infants might demonstrate more benefits for language development due to better readiness for active participation.

*H4:* Intervention efficacy may vary according to dyslexia risk.

It is explored whether the intervention benefits for language development are moderated by familial dyslexia risk. For example, the dyslexia-risk group can benefit more if ceiling effects are assumed in the no-risk group; on the other hand, genetic risk may compromise the risk group’s ability to benefit from the intervention (e.g., via reduced neuroplasticity in speech and language-related networks). These exploratory hypotheses are studied by confirming the parental dyslexia status and by investigating allele groupings in single-nucleotide polymorphisms of susceptibility genes associated with language, reading, and developmental dyslexia, analyzed from DNA samples of the infants and their biological parents.

*H5:* Social–emotional benefits of the interventions mediate the benefits for language development.

It is explored whether the experimental arm demonstrates greater social–emotional benefits than the control arm and whether these benefits mediate the benefits for language development. Social–emotional benefits are evaluated at the three assessment points with standardized parental questionnaires on infant and early childhood temperament, social–emotional/behavioral problems and delays, as well as parental wellbeing, stress, and interaction with the child.

*H6:* The music intervention will benefit music processing.

It is hypothesized that the development of music processing will be superior in the experimental (music) group compared to the control arm (circus), due to the main teaching aims of the music intervention. To this end, neural music processing will be evaluated with ERPs, particularly MMRs to changes in a melody, recorded at the three assessment points, and is expected to be more mature in the music group compared to the circus group after but not before the intervention. At follow-up assessment, behavioral musical abilities are additionally assessed with a custom-designed behavioral test battery, and better performance is expected in the music group compared to the circus group.

*H7:* The circus intervention will benefit motor abilities.

It is hypothesized that motor development, particularly gross motor development, is greater in the control (circus) arm than in the experimental arm (music) between the three assessment points, due to the main teaching aims of the circus intervention. Motor development is evaluated with customized parental questionnaires at baseline, post-intervention, and follow-up assessments, as well as with a standardized test at the post-intervention and follow-up assessments.

## Methods and analysis

2

### Participants

2.1

#### Participant recruitment and consent

2.1.1

The participants are infants from Finnish families from the greater Helsinki region, recruited between March 2024 and September 2025 by distributing paper flyers and digital advertisements via the project website, social media (Facebook, Instagram), local maternity clinics, and public events and lectures. Families can express their interest in participation via an electronic form on the project website or by contacting the trial coordinator via the project email. Participation is expected to be appealing to families due to the intervention, which is offered at no cost to all participating families and is similar to a self-paid infant–parent hobby. In order to achieve a sufficient sample size (see 2.1.3), recruitment will continue for approximately 1.5 years.

The trial coordinator screens the families for eligibility and the need for parental dyslexia testing (see 2.1.2) on the phone with the parent and, after receiving oral consent for participation from the parent, conducts stratification, randomization, and allocation of eligible infants to the two intervention arms (see 2.2).

One or both parents of the infant will be provided with a participant information sheet and data protection notice and will sign written informed consent for participation before starting the baseline assessment. This study is conducted at the University of Helsinki, Finland. The study has been approved by The University of Helsinki Research Ethics Committee in the Humanities and Social and Behavioral Sciences with the title “Infant and toddler age hobbies as support for language development (BusyBaby)” (public title translated from Finnish), and preregistered at ClinicalTrials.gov with the title “Language Development Deficits and Early Interactive Music Intervention—a Randomized Controlled Trial (BusyBaby)” (scientific title; NCT06261307, February 7th, 2024). Any important protocol modifications will be reported at the preregistration site.

#### Eligibility criteria

2.1.2

General inclusion criteria for the infants are that they must be 8–12 months old at the start of the intervention (recruited between 0 and 11 months) and must be born healthy and at term (gestational age of at least 37 weeks and birth weight of at least 2,500 g). Additionally, at least one caregiver living with the infant is required to be a native speaker of Finnish and to speak Finnish to the infant. General exclusion criteria for the infants include medication affecting the central nervous system, sensory deficits, and serious health conditions.

Families with (risk group) and without developmental dyslexia in one or both biological parents (no-risk group) are recruited. In the risk group, parental dyslexia is confirmed at enrollment in the study. To be included in the risk group, one or both biological parents must (1) suspect or state that they have dyslexia and (2a) either have a recent (< 5 years) clinical statement of dyslexia or, if it is not available, (2b) demonstrate reading problems since childhood in a clinical interview and current reading problems based on below-norm performance in a test battery [Finnish standardized test measuring speed and accuracy of oral text, word, and pseudo-word reading, and writing speed (Nevala et al., 2006)]. Parents who report clear reading problems in childhood and dyslexia in biological relatives are accepted into the risk group as compensated dyslexics, even with normative performance in the test. Exclusion criteria in the risk group include a diagnosis of a neurodevelopmental disorder other than dyslexia or developmental language disorder in either of the biological parents and, in the dyslexic parent, brain trauma in childhood that may indicate a non-heritable cause for the reading deficit, or an individualized school curriculum that may indicate broader developmental deficits.

In the no-risk group, exclusion criteria include suspected or diagnosed dyslexia or developmental language disorder in either of the biological parents, and a diagnosis of a neurodevelopmental disorder or severe neurological or psychiatric disorder in either of the biological parents. In both groups, at least one biological parent must be available to provide background information for the study. If only one biological parent is available, eligibility screening related to inherited risk factors is conducted based only on that parent.

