##### Language abilities

2.5.1.1

Language abilities will be assessed using two validated parental report instruments: The Infant–Toddler Checklist of the Communication and Symbolic Behavior Scales Developmental Profile [CSBS ITC (Wetherby and Prizant, 2002); Finnish version (Laakso et al., 2011)] and the standardized Finnish long form version of the MacArthur Communicative Development Inventories [Words and Gestures form, MCDI (Fenson et al., 1993); Finnish version (Lyytinen, 1999), Finnish Long Form version of the Communicative Development Inventories, FinCDI-LF]. Both methods have been normed for Finnish children and have shown to provide reliable information on the language skills of children [CSBS ITC (Laakso et al., 2011); FinCDI-LF (Lyytinen, 1999; Stolt et al., 2009)]. The CSBS ITC is a brief screening tool with three subscales (social, speech, and symbolic subscales) and a total score. The Words and Gestures form of the FinCDI-LF provides comprehensive information on children’s early receptive and expressive lexicons as well as on the development of early gestures. It gives scores separately for expressive and receptive vocabulary size and for the gestures scale for non-verbal communication.

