##### Language abilities

2.5.2.1

The standardized parental questionnaires (validated parental report instruments) CSBS ITC and MCDI/FinCDI-LF 16–30 mo will be re-administered to evaluate the language abilities at the follow-up assessment (Wetherby and Prizant, 2002; Laakso et al., 2011; Fenson et al., 1993; Lyytinen, 1999). The MCDI/FinCDI-LF 16–30 mo provides the size of expressive vocabulary and the mean length of the three longest utterances (in morphemes). The standardized language assessment test battery *Reynell Developmental Language Scales III (RDLS-III)* (Edwards et al., 1997; Reynell and Huntley, 2001); presented to the participants in Finnish (Kortesmaa et al., 2001) is conducted at post-intervention and follow-up assessment points and provides scores for expressive and receptive language abilities. It is relevant to acknowledge that at the post-intervention assessment point, the participants are still below the age range of the RDLS-III (younger than 2 years), and therefore, the scores obtained in this assessment will be treated with caution.

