#### Background variables and parent-reported activities

2.5.4

At baseline, a custom-made parental questionnaire is administered to collect basic information on the following background variables: child’s age, gender, family structure, living situation and daycare situation, language background and exposure, genetic risk factors for neurodevelopmental, neurological, and psychiatric conditions, socioeconomic status (indicated by parental education and current employment status), physical growth (weight and height at birth and their development), as well as healthcare and illnesses of the child. At post-intervention and follow-up assessment points, possible changes regarding family structure, living and daycare situation, language background and exposure, genetic risk factors, as well as physical growth (height and weight) and healthcare and illnesses of the child will be inquired.

At all three assessment points, custom-made parental questionnaires are additionally used to collect information on the frequency and intensity of the child’s musical activities (including joint singing, dancing, moving to music, and playing instruments at home, music listening, and exposure to music at home), musical background of the parents (including preferences, training, and listening habits), home literacy environment (including the amount of reading by parents, the amount of reading aloud to the child, the amount of children’s and adults’ books at home, frequency of library visits, and audio book listening), screen time, and all regular hobbies that the child attends.

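### Infants with a second home language are eligible, but FinCDI-LF vocabulary and RDLS-III capture Finnish only, and section 2.9 does not name the language-exposure data collected at baseline

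*Protocol article*

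**What the plan says.** **Eligibility (2.1.2).** The language rule is that "at least one caregiver living with the infant is required to be a native speaker of Finnish and to speak Finnish to the infant". Nothing restricts entry to Finnish-only homes or sets a floor on Finnish input.

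**Primary language measures (2.5.1.1).** One is "the standardized Finnish long form version of the MacArthur Communicative Development Inventories". On its scores: "It gives scores separately for expressive and receptive vocabulary size and for the gestures scale for non-verbal communication". The other is the CSBS ITC: "The CSBS ITC is a brief screening tool with three subscales (social, speech, and symbolic subscales) and a total score". On norms: "Both methods have been normed for Finnish children". ERPs and MMRs to speech sounds are also primary (2.5.1.2).

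**Secondary language test (2.5.2.1).** RDLS-III is given at post-intervention and follow-up, not at baseline, and is "presented to the participants in Finnish".

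**Exposure data (2.5.4).** The baseline questionnaire covers "language background and exposure, genetic risk factors for neurodevelopmental, neurological, and psychiatric conditions". The two later assessments ask about "possible changes regarding family structure, living and daycare situation, language background and exposure".

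**Analysis (2.9).** The primary contrast is time by arm. The section then names age, developmental status, dyslexia risk, genetic subgroups, morning or evening sessions, adherence, motivation, social structure and atmosphere, home activities and hobbies. Language exposure is not among them. It is not a stratification factor (2.2), and the limitations (3.1) do not discuss it.

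**The concern.** A word that an infant knows only in another language does not count on a Finnish inventory. For an infant with two home languages, a FinCDI-LF vocabulary score therefore reflects both how far language has developed and how much of the input is Finnish.

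A constant difference in level between multilingual and Finnish-only infants drops out of a change from baseline. A difference in growth does not. The intervention starts at about 8–12 months, when vocabulary is small, so most of the vocabulary being compared is acquired between the two assessments. It is plausible, though the article gives no data, that Finnish vocabulary grows more slowly in infants with less Finnish input. RDLS-III has no baseline score, so not even a level difference cancels there.

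Two things are at stake. The first is precision: exposure adds variance unrelated to treatment. The second is dilution: a benefit that shows up partly in the other language would be partly missed. The trial has little power to spare, with 75 and 79 infants at baseline (2.6) against the 100 per arm that the sponsor's own simulations call for (2.1.3).

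**Working it through.** **Inputs from the protocol article.** g = 0.31, alpha 0.05 (taken as two-sided), power 0.8, correlation 0.7, and 100 per arm from the mixed-model simulations (all 2.1.3). Infants with baseline data: 75 music, 79 circus (2.6).

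**Inputs assumed.** Share of infants with a second home language, p = 10–30%. Difference in their growth in Finnish score, D = 0.25–1.0 SD. The article gives neither.

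**Step 1: reproduce the plan's figure.** Treat time by arm as a comparison of change scores.
- Change-score variance = 2 × (1 − 0.7) = 0.6; SD = 0.775.
- n per arm = 2 × (1.960 + 0.842)² × 0.6 / 0.31² = 98.0, or 99 when rounded up conservatively. Power at 100 per arm is 0.80 (t) or 0.81 (normal approximation).

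The stated 100 per arm is reproduced, so this is a fair scale for what follows.

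**Step 2: power at the achieved size, no dropout, exposure ignored.**
- SE = 0.775 × √(1/75 + 1/79) = 0.775 × 0.1612 = 0.125.
- Power = Φ(0.31/0.125 − 1.96) ≈ 0.70.

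**Step 3: add variance from a growth difference.** Variance becomes 0.6 + p(1 − p)D².

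| p | D | Added variance | Increase on 0.6 | Power at 75/79 |
|---|---|---|---|---|
| 0.10 | 0.25 | 0.0056 | 0.9% | 0.695 |
| 0.10 | 0.50 | 0.0225 | 3.8% | 0.68 |
| 0.20 | 0.50 | 0.040 | 6.7% | 0.67 |
| 0.20 | 1.00 | 0.160 | 26.7% | 0.60 |
| 0.30 | 1.00 | 0.210 | 35.0% | 0.57 |

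Over the same range, the n needed for 0.8 power runs from 99 to 133 per arm.

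**Step 4: dilution, under a further assumption.** If only half the effect is visible in multilingual infants, the average effect is 0.31 × (1 − 0.5p). Power at 75/79 then runs from 0.65 (p = 0.10, D = 0.25) to 0.44 (p = 0.30, D = 1.0). The article gives no basis for the one-half, so this shows direction only.

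**Step 5: chance imbalance.** The SE of the arm difference in multilingual share is √[p(1 − p)(1/75 + 1/79)] = 0.048 to 0.074, a 95% range of about ±9 to ±14 percentage points. At D = 0.5 this moves the estimate by ±0.05 to ±0.07 SD. It is the Step 3 variance seen another way, is already inside the standard error, and must not be counted twice.

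**The case against.** The strongest reply is that this argues from silence. Section 2.9 does not claim that its list is complete, its footnotes and any analysis plan are not shown, and articles commonly leave covariate lists to such a plan. A reader might infer that the exposure data will go unused. The text does not support that, only that section 2.9 does not name them. What remains is that the article fixes an eligibility rule and a Finnish-only primary vocabulary measure that sit poorly together, and gives a long list of covariates and moderators without the one that connects them.

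Three other strong readings also fail:
- **That the scores measure exposure instead of ability.** They mix the two and still carry ability.
- **That all primary outcomes are affected.** CSBS ITC, the gestures scale and the ERPs are not Finnish word counts.
- **That the treatment effect is biased.** Chance imbalance under randomization is random error. Section 2.2 says the sequence is not concealed from the trial coordinator, but no imbalance in home language is reported.

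It is also fair to say that the rule guarantees some Finnish input and is a legitimate inclusive choice, that the range in the calculation is assumed, and that at its lower end nothing changes. Finally, the SD behind g = 0.31 may already contain this variation; the article does not say. In that case the numbers show what adjustment could gain rather than what is lost.

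**Conclusion.** The point holds for FinCDI-LF expressive and receptive vocabulary and for RDLS-III. In infants with a second home language these scores combine ability with Finnish exposure, and the time-by-arm contrast removes only the part that is constant over time. The consequence is lost precision and possible dilution.

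On the stated design values with no dropout, power falls from about 0.70 to between 0.695 and 0.57. This rests on an assumed multilingual share of 10–30%, an assumed growth difference of 0.25–1.0 SD, and a design SD that does not already include this variation. The sponsor can replace the assumed share with the actual one from the baseline questionnaire.

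**What to change.** In section 2.9, prespecify:

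1. **FinCDI-LF vocabulary models:** baseline Finnish exposure as a covariate together with its interaction with time. A main effect alone explains level, not growth, and would leave the time-by-arm contrast essentially unchanged.
2. **RDLS-III analysis:** baseline Finnish exposure as a covariate.
3. **Sensitivity analysis:** the same comparisons in infants exposed only to Finnish. This addresses dilution, which the covariate does not.

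Use the baseline value, which precedes the intervention, rather than the later updates. CSBS ITC, gestures and ERPs do not need this.

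The cost is one or two extra model parameters and one additional analysis in a smaller sample. The data are already collected, and fixing the choice now avoids making it after results are seen.

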#### Sample size

2.1.3

The target maximum sample size is *N* = 200 infants. To reach a balanced sample, the aim is to recruit 30–50 participants for each stratum (see 2.2). A power analysis indicated that 50 participants per intervention arm are needed to evaluate the primary outcome measures, given a repeated measures ANOVA with a two-within (time of assessment: baseline vs. post-intervention) x two-between (intervention arms) design, a small effect size, Hedge’s g of 0.31 [based on the meta-analysis (Neves et al., 2022)], an alpha level of 0.05, a power of 0.8, and an expected correlation of 0.7 between the repeated measures.

Based on our previous longitudinal intervention study [see Virtala et al. (2022), Virtala and Partanen (2018), and Virtala et al. (2023), where 76% of the original sample recruited at birth participated in EEG and behavioral tests at 28 months], and given the engaging and rewarding nature of both intervention arms and the lack of a passive control group, we expect a low drop-out rate of a maximum of 20% for the primary outcome measures, including baseline and post-intervention assessments. This percentage includes families who will refuse participation before completing post-intervention assessments or who will not successfully complete some of the baseline or post-intervention assessments. Therefore, we assume that a sample size of *N* = 120 will be sufficient for reliably evaluating the primary outcomes of the interventions in the repeated measures ANOVA framework. However, it is relevant to note that this sample size is not optimal for probing the interaction of intervention arm x time in the linear mixed models or for the additional analyses (including, e.g., subgrouping based on participant characteristics or mediation analyses, see 2.9). To additionally calculate sufficient sample sizes per intervention arm for the planned linear mixed models, specifically considering the studied interaction of intervention arm x time, simulations were run according to Caldwell et al. (2022) and Kumle et al. (2021). These simulations suggested a larger required sample size of 100 per arm in order to ensure a power of 0.8, considering the values described above. We therefore aim for a sample size between 120 and 200, as large as practically possible within the 1.5-year time frame for participant recruitment.

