### Trial timeline

2.6

Recruitment started in March 2024, and the first family was enrolled in the study after randomization on 13 June 2024. Recruitment ended on 30 September 2025. The interventions are conducted between September 2024 and March 2026 (estimate). Altogether, 10 music interventions and 10 circus interventions will be conducted so that one music intervention and one circus intervention start nearly every month between September 2024 and October 2025 (estimate). The planned duration of all interventions is 5–7 months; however, all interventions consist of 20 weekly sessions with a fixed time (the number of canceled sessions and break weeks varies between interventions for practical reasons). Outcome measures will be collected at baseline (between August 2024 and September 2025), 6 months (post-intervention; between March 2025 and March 2026, estimate), and 1.5 years (follow-up, one year after post-intervention; between March 2026 and April 2027, estimate). Thus, data collection for primary outcome measures is estimated to be completed by March 2026 and for all outcome measures in April 2027.

By the end of recruitment and baseline assessments on 30 September 2025, 184 participants had been randomized to the study after providing oral consent. Of these, 154 participants had attended the baseline assessments and provided written informed consent (separate n’s according to strata: dyslexia-risk boys/dyslexia-risk girls/no risk boys/no risk girls *N* = 32/42/41/39; according to intervention arm: music/circus *N* = 75/79) with an average age of 10.17 months (SD 1.43, range 6.73–13.13; according to intervention arm: music/circus 10.18/10.14 months) at the first intervention session. Participants who were unable to attend the intervention sessions after providing written consent were nevertheless invited to all assessment points (see 2.9) unless they refused participation altogether. By the end of recruitment, one participating family with written consent had refused participation after the baseline assessment.

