### Data analysis

2.9

All analyses will preferably be conducted with intention-to-treat analysis, including all participants regardless of attendance rate and whether they completed the intervention. However, when deemed necessary, for example, due to the amount of missing data, the intention-to-treat analyses can be complemented by per-protocol analyses, i.e., with only those participants included who successfully completed the intervention (see 2.4).

In the primary analyses, the efficacy of the trial will be evaluated by investigating changes in the primary outcome measures between baseline and post-intervention assessments, based on an interaction between time (baseline vs. post-intervention) and intervention arm (music vs. circus).^2^ Main analysis methods will be linear mixed models and repeated-measures ANOVAs, with statistical significance defined as *p* < 0.05 and appropriate adjustments correcting for multiple comparisons. Linear mixed models are well-suited for accommodating missing data that may occur between assessment points through the use of maximum likelihood estimation, which allows all available data to contribute to the estimation of model parameters under the assumption of missing at random.

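### Section 2.1.3 gives 50 per arm and N = 120 as sufficient, but the primary arm-by-time test needs about 99–100 analysed infants per arm whether run as ANOVA or mixed model

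*Protocol article*

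**What the plan says.** Protocol article, 2.1.3 (Sample size), gives a first requirement: "A power analysis indicated that 50 participants per intervention arm are needed to evaluate the primary outcome measures". Its basis is "given a repeated measures ANOVA with a two-within (time of assessment: baseline vs. post-intervention) x two-between (intervention arms) design", with "a small effect size, Hedge’s g of 0.31" and "an alpha level of 0.05, a power of 0.8, and an expected correlation of 0.7 between the repeated measures". After allowing for at most 20% drop-out, the section concludes that a total of 120 "will be sufficient for reliably evaluating the primary outcomes of the interventions in the repeated measures ANOVA framework".

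The same paragraph then qualifies this. It says 120 is not optimal for the arm-by-time interaction in linear mixed models, and reports simulations run with the values already given: "These simulations suggested a larger required sample size of 100 per arm in order to ensure a power of 0.8". The target is set between 120 and 200, as large as is practical in the recruitment window.

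Section 2.9 (Data analysis) defines the primary efficacy evaluation as change from baseline to post-intervention, "based on an interaction between time (baseline vs. post-intervention) and intervention arm (music vs. circus". The main methods named are linear mixed models and repeated-measures ANOVAs.

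Section 2.6 (Trial timeline) reports that recruitment has closed. Of 184 infants randomized, "154 participants had attended the baseline assessments and provided written informed consent", 75 in the music arm and 79 in the circus arm.

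**The concern.** One paragraph gives two requirements, 50 and 100 per arm, from one set of inputs, and attributes the gap to the choice of model. For this design the choice of model does not produce such a gap. The ANOVA figure is the one used to call 120 infants sufficient for the primary outcomes, yet the primary test is the interaction, to which the larger figure applies.

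What is at stake is how the result is read. Someone comparing 154 infants at baseline with a sufficient total of 120 would think the trial comfortably powered at the planned effect. If it is not, a non-significant interaction could be over-read as evidence that music has no specific benefit.

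**Working it through.** **Inputs.** From 2.1.3: g = 0.31, alpha = 0.05, power 0.80, r = 0.7, drop-out at most 20%. From 1.3: 1:1 allocation. From 2.6: 184 randomized, 154 at baseline (75/79). Assumptions, because the document is silent: g is the between-arm difference in change in raw-score SD units, and alpha is two-sided.

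**Equivalence.** With two time points, two arms and complete data, the ANOVA interaction, the random-intercept mixed-model interaction and a two-sample t test on change scores are the same test. All can be powered through the change score.

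**Required n.**
- SD of change = sqrt(2 × (1 − 0.7)) = 0.775.
- Standardized effect = 0.31 / 0.775 = 0.400.
- n per arm = 2 × (1.960 + 0.842)² × 0.775² / 0.31² = 98.0, rounded up to 99. The exact noncentral t also gives 99.

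This reproduces the protocol's 100 per arm (power 0.804 at 100; 0.80 by simulation).

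**Attempts to reproduce 50 per arm for a between-arm comparison.**

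| Reading | Result for 80% power |
|---|---|
| Change score, two-sided | 99 per arm |
| Change score, one-sided | 78 per arm |
| Baseline-adjusted (ANCOVA), two-sided | 84–85 per arm |
| Baseline-adjusted (ANCOVA), one-sided | 66 per arm |
| Post score only | 164 per arm |
| Arm effect on the mean of both times | about 139 per arm |
| f = 0.31/2 = 0.155 entered as the interaction effect | about 51–52 in total |

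A pre-post paired test within a single arm needs 51 infants. The 50 may therefore come from a within-arm effect, or from a total read as a per-arm number; the document does not show which. For 50 per arm to give 80% power on the interaction, r would have to be about 0.85, or the effect about 0.43–0.44 SD.

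**Power for the interaction (noncentral t, two-sided 0.05).**

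| Analysed | Power |
|---|---|
| 50 per arm | 0.51 |
| 60 per arm (N = 120, no loss) | 0.58 |
| 48 per arm (N = 120 less 20%) | 0.49 |
| 80 per arm (N = 200 less 20%) | 0.71 |
| 100 per arm | 0.80 |

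**Drop-out step.** 120 × 0.8 = 96, short of the 100 required; 100 / 0.8 = 125. The figure of 120 matches 100 × 1.2. This alone matters little (power 0.51 against 0.49). More important, the 100 per arm is not inflated at all: 200 / 0.8 = 250 would have to be randomized, above the stated maximum of 200.

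**Attained sample.** The detectable difference is the value giving 80% power.

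| Case | Analysed | Power | Detectable difference |
|---|---|---|---|
| All with baseline | 154 (75/79) | 0.69 | 0.35 SD |
| 184 randomized less 20% | 147 | 0.67 | 0.36 SD |
| Pessimistic: a further 20% off 154 | 123 | 0.60 | 0.39 SD |

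None of these figures allows for several primary outcomes or for delivery in groups; either would generally lower power.

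**The case against.** The strongest reply is that the paragraph already discloses the problem. The sufficiency claim is limited to the ANOVA framework. The next sentence calls 120 not optimal for the mixed-model interaction, 100 per arm is printed, and the target range is drawn from it. Section 3.1 also warns that several primary variables raise the risk of underpowered analyses. This stands as mitigation, and a reader should not infer that the protocol hides the larger requirement. It does not remove the error: the caveat presents low power as a property of the mixed model, when the ANOVA interaction has the same power.

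It is also tempting to say that the trial has failed an 80% claim. The documents do not support that. For the interaction, 80% is tied only to 100 per arm; it is claimed neither for 154 infants nor for the whole range from 120 to 200.

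A third reply is that the text never says which ANOVA effect the 50 refers to, so it might be a within-arm change. If so, the arithmetic may be sound, but the effect is not the one section 2.9 tests, and the sufficiency statement still fails.

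A fourth is that the scale of g is undefined. If f = 0.155 is entered directly as the interaction effect, 50 per arm would have 98% power. That reading does not return 50 per arm either, and it conflicts with the protocol's own 100 per arm. Exact equivalence of the tests also needs complete data and an unadjusted model. Sections 2.9's maximum-likelihood handling of missing data and added factors could shift the figures somewhat, but nothing in the document suggests they would halve the requirement.

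Lastly, power of about 60% should not be presented as the expected case. The 20% allowance covers refusals and incomplete assessments up to post-intervention, and 30 of the 184 randomized (16%) were already gone before baseline. Taking a further 20% off 154 probably counts some loss twice.

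**Conclusion.** The 50-per-arm figure and the statement that N = 120 is sufficient are wrong as written for the primary test. That test needs about 99–100 analysed infants per arm in either framework, roughly twice the number given for the ANOVA. At the planned effect, 120 infants give between 49% (20% loss) and 58% (no loss) power. The stated maximum of 200 gives 71% after the plan's own 20% loss.

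This rests on g = 0.31 being the between-arm difference in change in raw SD units, r = 0.7, two-sided alpha of 0.05 and complete data. The first is an assumption, supported by its reproducing the protocol's simulation result. How the 50 arose cannot be settled from the document.

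**What to change.** In 2.1.3:

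1. Correct the 50-per-arm and N = 120 statements to say that the primary arm-by-time interaction needs about 99–100 analysed infants per arm, whether tested by repeated-measures ANOVA or by mixed model. If the 50 was computed for another effect, name that effect and say it is not the primary test.
2. Define the scale of g (difference in change, in raw-score SD units, if that was meant) and the sidedness of alpha.
3. Correct the drop-out step (100 / 0.8 = 125) and say that the 100 per arm is a number analysed, not recruited.
4. Restate power and detectable difference for the attained sample: 69% and 0.35 SD if all 154 are analysed; 67% and 0.36 SD if 147 are; about 60% and 0.39 SD labelled as a pessimistic case.

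The cost is a rewording and a less favourable stated figure. No extra enrolment and no change to the analysis or conduct of the trial is asked for.
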